#### Sample size

We design a superiority trial with a ratio of 1:1. The primary outcome is the mean change of BCVA at week 48 as compared to the baseline. After reviewing some literature, the mean change of BCVA in the test group is expected to increase by 10.1 letters measured by ETDRS chart, which in the control group is expected to increase by 8.2 letters [39, 40]. *n*_*c*_ is the participants’ number in each group. σ (standard deviation of the two groups) = 4. *Z*_1−*α*_ = 1.96, when *α* = 0.025; *Z*_1−β_ = 0.84, when *β* = 0.2. Δ = 0, *K* = 1, μ_T_ = 10.1, μ_C_ = 8.2. We calculate it by the PASS software; there are 71 cases in each group. Considering a 20% drop-out rate, there are 89 cases in each group and a total of 178 cases in both groups. Thus, we plan to recruit 180 participants in total (30 cases in every center, 15 cases in each group). The sample size calculation formula is as follows [41]:
$$ {n}_c=\frac{{\left({Z}_{1-\upalpha}+{Z}_{1-\upbeta}\right)}^2{\sigma}^2\left(1+1/K\right)}{{\left({\mu}_T-{\mu}_C-\Delta \right)}^2} $$

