#### Statistical methods

All the efficacy and safety analyses will be conducted within the full analysis set (FAS) according to the intention-to-treat principle, with all randomly assigned participants included. Last-observation-carried-forward method will be applied in the missing values. We will conduct the per-protocol set (PPS) analysis to compare the results from FAS and PPS, and safety set (SS) will be used for the safety evaluation. Data from the six centers will be combined for statistical analysis of the primary and secondary outcomes as well as adverse events. Demographic, eye examination, and laboratory characteristics will be calculated at baseline, intervention, and follow-up period. The mean ± standard deviation will be chosen for continuous variables and the comparison between the two groups will be analyzed by *t* tests with normal distribution. Non-parametric Mann-Whitney-Wilcoxon test will be used for the comparison of data with non-normal distribution. Categorical variables will be compared using *χ*^2^ statistics, while the Fisher exact test will be used when the theoretical frequency is less than 5 in more than 25% of the cells. In order to control the center and baseline effects, covariance analysis will be applied for the intergroup comparison with continuous variables and Cochran-Mantel-Haenszel test for categorical variables. All statistical tests are unilateral tests; *P* < 0.05 means statistically significant. All statistical analyses will be performed by using SPSS V.19.0.

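### The trial is sized at one-sided 0.025 but judged at one-sided 0.05, which doubles the nominal false-positive rate of the primary test

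*Protocol article*

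**What the plan says.** Two sections of the protocol article fix the error level of the primary comparison.

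- **Sample size.** The design is stated as "We design a superiority trial with a ratio of 1:1", with a margin of zero. The inputs are "1.96, when *α* = 0.025" and "0.84, when *β* = 0.2", a gain of 10.1 letters on test and 8.2 on control, and "σ (standard deviation of the two groups) = 4". The printed formula uses Z(1−α), not Z(1−α/2), so α = 0.025 is a one-sided level. The result is "there are 71 cases in each group", raised to 89 for 20% drop-out and then to 180 in total.
- **Statistical methods.** The decision rule is: "All statistical tests are unilateral tests; *P* < 0.05 means statistically significant". It covers every test, so it includes the primary outcome.

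The article nowhere sets a separate 0.025 threshold for the primary outcome, describes the 0.05 as two-sided, or explains why the two levels differ.

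**The concern.** A one-sided test at 0.025 rejects when the standardised difference exceeds 1.96; at 0.05 it rejects above 1.645. The sample size was calculated with the first value, and the stated rule for declaring significance uses the second. Both cannot describe the same primary test.

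What is at stake is the strength of the superiority claim. A result with a one-sided P between 0.025 and 0.05 is positive under Statistical methods and negative at the level behind the sample size. While both statements stand, the reading could be chosen after the data are seen. A reader who takes the sample-size paragraph as the design would also believe that the claim is protected at 2.5% when it is not.

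**Working it through.** **Inputs (Sample size section).** Difference 10.1 − 8.2 = 1.9 letters; SD 4 in both groups; 1:1 allocation (K = 1); margin 0; power 80% (Z = 0.84); α = 0.025 (Z = 1.96); drop-out 20%.

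**Step 1: reproduce the plan's figure.** The printed formula gives

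n = (1.96 + 0.84)² × 4² × 2 / 1.9² = 7.84 × 32 / 3.61 = 69.5, so 70 per group.

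This is a normal approximation. With the noncentral t distribution at one-sided 0.025, power is 0.797 at 70 per group and 0.8025 at 71. So 71 is the first size to reach 80%, as stated. Drop-out: 71 / 0.8 = 88.75, so 89 per group and 178 in total, also as stated.

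**Step 2: repeat at the level in Statistical methods.** At one-sided 0.05,

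n = (1.645 + 0.842)² × 32 / 3.61 = 54.8, so 55 per group.

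The noncentral t version needs 56, or 56 / 0.8 = 70 after drop-out. The stated 71 and 89 therefore cannot come from one-sided 0.05. They match one-sided 0.025 or, equivalently, two-sided 0.05.

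**Step 3: type I error.** 0.05 / 0.025 = 2. The nominal rate in the direction of benefit is exactly twice the design level and equals that of a two-sided 10% test.

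**Step 4: smallest difference declared significant** (unadjusted t-test, SD 4).

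- 71 per group: standard error = 4 × √(2/71) = 0.671. With t(140) of 1.977 and 1.656, the limits are 0.671 × 1.977 = 1.33 letters and 0.671 × 1.656 = 1.11 letters.
- 90 per group: standard error = 4 × √(2/90) = 0.596. The limits are 1.18 and 0.99 letters.

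**Step 5: power at a true difference of 1.9 letters** (noncentral t).

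| Per group | One-sided 0.025 | One-sided 0.05 |
|---|---|---|
| 71 | 0.803 | 0.879 |
| 90 | 0.887 | 0.937 |

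At 71 per group, the chance of a result that the two rules classify differently is 0.879 − 0.8025 = 0.077 if the assumed effect is real. If the product is inert it is 0.05 − 0.025 = 0.025, which is half of all false positives under the looser rule.

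**The case against.** The strongest reply is that the word unilateral is a slip. The same sentence covers χ² tests and covariance analysis, whose usual test statistics have no direction. If P < 0.05 is read from those, the error in the direction of benefit is 2.5% and agrees with the sample size. That reading is plausible. But the text says the opposite, and the one-sided Z(1−α) in the sample-size formula fits a deliberate one-sided approach. If it is a slip, the same correction is needed.

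Four smaller points deserve a fair hearing.

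- **Per-test rate.** The 5% is nominal and applies to one test. The Abstract and the Primary outcome section name both week 24 and week 48, whereas the Sample size section names week 48 only. How that is settled affects the overall rate, but it is a separate question. This limit stands.
- **Which n.** The main analysis takes in everyone randomised and carries the last observation forward, so 90 per group is closer to what will be analysed than 71. The power gap is then about 5 percentage points (0.887 against 0.937), not 8. This stands too, but the doubling of the error rate does not depend on n.
- **Adjusted analysis.** The plan also specifies covariance analysis for centre and baseline, so the thresholds in letters are illustrative. Agreed.
- **An unseen analysis plan.** It may settle the level. But this is not something left out for later: the article states a decision rule, and that rule conflicts with its own design level. An analysis plan that followed it faithfully would carry the looser rule forward.

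**Conclusion.** The concern holds. The two sections contradict each other, and the only decision rule that the article states is the looser one. Applied as written, it sets the nominal type I error of the primary superiority test at 0.05 instead of the design value of 0.025.

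The doubling needs no assumption beyond a literal reading of the stated rule. The thresholds in letters and the power figures also rest on the plan's SD of 4, its assumed difference of 1.9 letters and an unadjusted two-sample t-test. The sample size itself is correct for one-sided 0.025. This must be fixed, because the fault lies in the rule that decides the primary claim.

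**What to change.** Replace the last part of the testing rule in Statistical methods with: tests are two-sided at the 0.05 level, and differences are reported with two-sided 95% confidence intervals. For the primary outcome, one-sided testing at 0.025 is equivalent and agrees equally well with the Z of 1.96 in the Sample size section. The intervals are good practice and are not needed to remove the contradiction.

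The change is one sentence in the protocol or analysis plan, made and dated before unblinding. No patients are added, because 71, 89 and 180 already assume this level. Version 2.0 of the protocol has ethics approval according to Trial status, so the change may have to be filed as an amendment.

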### Quality supervision and management

#### Request for researchers

Researchers or physicians will receive pre-clinical systematic training and get a full understanding of the protocol details, and they should possess the qualifications and ability to carry the study on and not be changed constantly.

#### Quality control of laboratory

Every center should offer researchers suitable medical equipment and emergency facilities. Laboratory, Medical Examination Center and other related departments will be established quality control and uniform standard operating processes. A certain item will be in charged by a special person.

#### Measures for study/treatment agents and compliance of participants

Mingjing granule and placebo will be manufactured by the same pharmaceutical factory and distributed by a trained staff in each center. Compliance of participants will be inspected by the method of drugs notation, and they will be asked to bring drugs last time in order to calculate the number. The formula is as follows:
$$ \mathrm{Compliance}=\left[\left(\mathrm{dispensing}-\mathrm{remaining}\right)/\mathrm{dispensing}\right]\times 100\% $$

#### Monitoring and inspection

A trial coordinating group will be established, which is responsible for the implementation of the trial, and they will visit each center regularly to check the progress of the trial, examine CRF, verify the storage of investigational agents, and record of data.

## Discussion

The medicinal herbal compound (fufang) is the most commonly used treatment approach of TCM in China. To the best of our knowledge, there are few high quality clinical studies that investigate the efficacy and safety of herbal compound in the treatment of AMD. Compared with previous studies [33–37, 39], this trial has more clinical research centers, clearer diagnostic criteria, a more rigorous methodology, and longer follow-up period.

Though the exact pathogenesis remains unclear, it is generally accepted that AMD is multifactorial disease related to environmental factors, genetic background, and parainflammation. Recent studies have found that autophagy dysfunction in RPE cells, cellular senescence, and abnormal immune-inflammatory responses play key roles in the pathogenesis of AMD. Neovascularization is an intermediate pathological phenomenon of nAMD; intravitreal injection of anti-VEGF agents is not an etiological treatment. It is easy to relapse after drug withdrawal [42]. Due to the multifactorial and complex nature of the disease, it may delay the process of AMD more effectively and obtain better clinical efficacy if multi-target effect could be achieved simultaneously. Unlike the single ingredient of western medicine, the composition of compound formula is very complex. Generally, a TCM compound formula is composed of several herbs; each herb normally has many ingredients, and multiple ingredients simultaneously act on multi-targets; a formula is a complex biologic active network [43].

Mingjing granule consists of Radix Astragali (huangqi), *Salvia miltiorrhiza* root (danshen), *Lycium barbarum* (gouqizi), *Eclipta alba* (mohanlian), Pollen Typhae (puhuang), and *Cirsium japonicum* (daji). Each herb in the formula has its bioactivities. For example, Radix Astragali is one of the most widely used traditional Chinese herbal medicines. It is used as immune stimulant, tonic, antioxidant, hepatoprotectant, diuretic, antidiabetic, anticancer, and expectorant [44]. *Salvia miltiorrhiza* root has been used for clinical treatment of various microcirculatory disturbance-related diseases for a long time. It contains many active water-soluble compounds, including protocatechuic aldehyde, 3,4-dihydroxyphenyl lactic acid, and salvianolic acid B. These compounds, as well as water-soluble fraction of *Salvia miltiorrhiza* root extract (SMRE), have an ability to scavenge peroxides and are able to inhibit the expression of adhesion molecules in vascular endothelium and leukocytes. Moreover, lipophilic compounds of SMRE also prevent the development of vascular damage [45]. *Lycium barbarum* (LB) is a renowned functional food and medicinal plant in Southeast Asia. Research data suggested that LB may exert neuroprotective effects and may aid in preventing neurodegenerative disease [46]. According to TCM theory raised from thousands of years of clinical practice, compatibility of medicinal herbs can strengthen the therapeutic efficacy and attenuate the toxicity of major component through drug-drug interaction. In this study, we will examine the efficacy and safety of Mingjing granule for nAMD patients. Our previous studies have shown that Mingjing granule could inhibit laser-induced CNV formation and development in BN rats through multi-targeting effects. Results from the pilot clinical study also showed that Mingjing granule could stabilize the patients’ visual acuity and reduce the area of retinal hemorrhage and exudation. And, no adverse effects have been observed through its clinical use, and toxicology studies in mice and rats support the safety of the proposed dose. These data support Mingjing granule as an alternative and complimentary therapy for CNV-associated disorders.

In summary, this protocol describes a randomized controlled trial conducted in 6 centers to evaluate the efficacy and safety of Mingjing granule in the treatment of AMD. If results of this trial demonstrates that Mingjing granule combined with ranibizumab has better efficacy, less injection times, and lower cost and good safety, it will provide useful clinically information for AMD and offer patients and ophthalmologists a new treatment option.

### Trial status

The updated version of trial protocol (version 2.0, 4 August 2020) has been reviewed and approved on 12 August 2020(YKEC-KT-2020-009). Recruitment will start in October 2020 and is expected to finish in March 2021.

## Data Availability

The datasets analyzed during the current study are available from the corresponding author on reasonable request.

## Abbreviations

nAMD: Neovascular age-related macular degeneration
anti-VEGF: Anti-vascular endothelial growth factor
TCM: Traditional Chinese medicine
AMD: Age-related macular degeneration
CNV: Choroidal neovascularization
hRPE: Human retinal pigment epithelium
PEDF: Pigment epithelium-derived factor
BN: Brown Norway
BMCs: Bone marrow-derived cells
SPIRIT: Standard Protocol Items: Recommendations for Interventional Trials
BCVA: Best-corrected visual acuity
ETDRS: Early treatment diabetic retinopathy study
OCT: Optical coherence tomography
AST: Aspartate transaminase
ALT: Alanine transaminase
PrONTO: Prospective OCT imaging of patients with neovascular AMD treated with intraocular ranibizumab
CRT: Central retinal thickness
CRF: Case report form
RPE: Retinal pigment epithelium
ALP: Alkaline phosphatase
γ-GT: Gamma-glutamyl transpeptidase
TBIL: Total bilirubin
Cr: Creatinine
ECG: Electrocardiogram
FAS: Full analysis set
PPS: Per-protocol set
SS: Safety set
SMRE: *Salvia miltiorrhiza* root extract
LB: *Lycium barbarum*
